**Acceptability**							
	Satisfaction	Client Satisfaction Questionnaire [108] assesses patient satisfaction with the program; percentage of participants with scores (minimum=3, maximum=12) above the scale’s midpoint		≥70%=good, ≥80%=excellent		After the intervention	
	Program attendance	Percentage of participants who attend ≥6 out of 8 sessions		≥70%=good, ≥80%=excellent		After the intervention	
	Perceived improvements	Modified Patient Global Impression of Change [109] asks participants about perceived improvements in cognitive function, lifestyle, and emotional well-being outcomes; percentage of participants who report improvement in each outcome domain (ranging from 1=*very much worse* to 7=*very much improved*)		≥70%=good, ≥80%=excellent		After the intervention and at 6-month follow-up	
**Appropriateness**							
	Credibility and expectancy	Credibility and Expectancy Questionnaire [110] assesses participant perceptions of the treatment as believable, convincing, and logical; percentage of participants with scores (minimum=3, maximum=27) above the scale’s midpoint		≥70%=good, ≥80%=excellent		Before the intervention	
**Fidelity**							
	Therapist fidelity	Percentage of sessions in which the study clinician completed an audio recording, progress note, and checklist with 100% of the content delivered (confirmed by blinded RA independently coding a random 10% of audio-recorded sessions)		≥75%=good, 90%=excellent		Study completion	
	Study procedures	Fidelity of staff to the study procedures as calculated by the frequency of protocol deviations		<5 deviations=good, 0 deviations=excellent		Study completion	
Patient safety			Number of self-reported adverse events		Mild in ≤10% of participants=good, none=excellent		Study completion

**Table 2 table2:** Study measures and constructs. Demographic and clinical characteristics are assessed before the intervention. All other measures are assessed before the intervention, after the intervention, and at 6-month follow-up.

Measure and description		Scoring	Psychometric evidence
**Demographic characteristics**			
	Age, gender, biological sex, race, ethnicity, education, income, occupation, marital status, living situation, and languages spoken	—^a^	—
**Clinical characteristics**			
	Mental health history, medical history, height, weight, Lifestyle for Brain Health (LIBRA) score [111-116], SCD^b^ diagnosis, medications and supplements taken for memory	—	—
**Cognitive function**			
	Cognitive Function Index [117], a 14-item measure assessing self-report of SCD across daily functions	1 (*yes*) to 0 (*no*) cognitive changes compared to 1 year ago; higher total scores (minimum=0, maximum=14) indicate greater SCD complaints	Adequate internal consistency and validity for older adults [118-120]
	Repeatable Battery for the Assessment of Neuropsychological Status (RBANS) [121], a comprehensive assessment that includes measures of visual, verbal, and numeric associative memory properties and provides a measure of global cognition	Higher *z* and index scores (minimum=0, maximum=160) indicate greater global and domain-specific cognitive functioning	Clinically valid [121] and high internal reliability among older adults [122]
**Physical activity**			
	PROMIS^c^ Physical Function [123]*,* an 8-item self-report of daily physical functioning	5-point scale ranging from 1=*unable to do* to 5=*without any difficulty*; higher T-scores indicate greater physical function and lower disability	Acceptable construct validity for older adults, sensitive to change during intervention studies, and excellent internal reliability [123,124]
	Godin Leisure-Time Exercise Questionnaire [125], a 3-item self-report of the frequency of engagement in light, moderate, and vigorous physical activity	Number of times per week engaged in activity; higher scores indicate greater frequency of physical activity for each intensity level	Good construct validity [126] and relatively reliable [127]
	Change in step count, measured via the Garmin Vivosmart 5 [128] (change in average step count during the 7 days preceding before the intervention assessment, throughout the intervention period, and 7 days at 6-month follow-up)	Higher step count totals indicate greater physical activity levels (walking)	Low actigraphy-measured step count is correlated with AD/ADRD^d^ risk and cognitive decline [129]; MCID^e^=600 to 1100 steps [130]
**Sleep**			
	Pittsburgh Sleep Quality Index [131], a 9-item self-report of sleep patterns and overall quality	Combination of 4-point scale ranging from 1=*not during the past month, very good* to 4=*≥3 times per week, very bad* and open responses; total scores range from 0 to 21, with a score of ≥5 indicating clinically significant sleep disturbance	Prior research supports the Pittsburgh Sleep Quality Index in older adults; high test-retest reliability, fair internal reliability [132], and good validity [133]
	Change in total sleep time, measured in minutes via the Garmin Vivosmart 5 [128] (change in total sleep time during the 7 days preceding before the intervention assessment, throughout the intervention period, and 7 days at 6-month follow-up)	Higher total minutes indicate greater sleep time	Poor actigraphy-measured sleep is correlated with AD/ADRD risk and cognitive decline [134]; MCID=40-minute increase [135]
**Mediterranean diet**			
	Mediterranean Eating Pattern for Americans Screener [131,136], a 16-item self-report of adherence to Mediterranean dietary recommendations	Participants earn 1 point for each food within the recommended serving size (range=0-16); higher total scores (minimum=0, maximum=21) indicate greater adherence to the Mediterranean diet	Poor internal reliability [131,136]; however, brief self-reports of the Mediterranean diet are limited
**Alcohol and tobacco use**			
	PROMIS Alcohol Use [137]*,* a 7-item self-report of at-risk drinking	5-point scale ranging from 1=*never* to 5=*almost always*; higher T-scores indicate greater problematic alcohol use	High convergent validity [137] and modest test-retest reliability [138]
	CDC^f^ Behavioral Risk Factor Surveillance System questionnaire concerning tobacco use [139]*,* a 2-item self-report of tobacco use history and current frequency of use of 6 common tobacco products	5-point scale ranging from 1=*less than once a month* to 5=*daily or almost daily*; higher scores indicate greater tobacco use	—
**Social functioning**			
	PROMIS Loneliness [140], a 5-item self-report of perceived loneliness	5-point scale ranging from 1=*never* to 5=*always*; higher T-scores indicate greater perceived loneliness	Good internal and test-retest reliability [141]
	Social Engagement and Activities Questionnaire [142], a 10-item self-report of general and social-group activities	6-point scale ranging from 1=*not at all* to 6=*every day*; higher total scores (minimum=0, maximum=50) indicate greater participation in socially engaging activities	High convergent validity for older adults [142]
	PROMIS Satisfaction with Social Roles and Activities [143], an 8-item self-report of satisfaction with ability to perform social activities and meet social needs	5-point scale ranging from 1=*not at all* to 5=*very much*; higher T-scores indicate greater satisfaction with social roles and activities	High reliability and acceptable item-total correlations [144]
**Mental activity**			
	Memory Compensation Questionnaire [145], a 44-item measure assessing the use of cognitive compensatory strategies for actual or perceived memory loss; the external and internal subscales (12 items) relevant to the MHB^g^ program are extracted	5-point scale ranging from 1=*never* to 5=*always*; higher total scores (minimum=0, maximum=65) indicate greater use of external and internal memory compensation strategies	Good internal validity among older adults [145]
	Measure of cognitive activities (adapted from Geda et al [146]), a 10-item self-report measure that assesses the extent to which an individual engaged in mentally stimulating and social activities over the past week	5-point scale ranging from 1=*never* to 5=*every day*; higher total scores (minimum=0, maximum=10) indicate greater participation in cognitively stimulating activities	Good test-retest reliability [147] and adequate construct validity [148]
**Depression and anxiety**			
	PROMIS Depression [149]*,* a 4-item measure assessing negative mood, views of self, engagement in daily living, and social components	5-point scale for depressive symptoms ranging from 1=*never* to 5=*always*; higher T-scores indicate greater depression	High reliability estimates among diverse older adults and clinically valid [150,151]
	PROMIS Anxiety [149]*,* a 4-item measure assessing fear, worry, hyperarousal, and somatic symptoms	5-point scale for anxiety symptoms ranging from 1=*never* to 5=*always*; higher T-scores indicate greater anxiety	High reliability estimates among diverse older adults [150] and strong validity [152]
**Mindfulness**			
	Applied Mindfulness Process Scale [153]*,* a 15-item instrument that measures the frequency of mindfulness practice	5-point scale ranging from 1=*never* to 5=*almost always*; higher total scores (minimum=0, maximum=60) indicate greater use of daily mindfulness activities	Strong internal consistency reliability and item-total reliability [153]
**Self-regulation**			
	Emotion Regulation Questionnaire [154], a 10-item self-report of emotion regulation strategies, both in how emotions are felt and expressed	7-point scale ranging from 1=*strongly disagree* to 7=*strongly agree*; higher total scores (range 10-70) indicate greater tendency to regulate emotions using cognitive reappraisal and expressive suppression strategies	Fair internal reliability among older adults [155] and strong validity [156]
	Cognitive Control and Flexibility Questionnaire [157], an 18-item self-report of control over unwanted experiences	4-point scale ranging from 1=*seldom or never* to 4=*almost always*; higher total scores (minimum=13, maximum=52) indicate greater daily use of cognitive control and flexibility	Excellent internal consistency and good construct validity in a community sample [157]

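### Table 2 scores emotion regulation as one total over two strategies, and six other rows print score ranges that do not follow from their own items and anchors

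*Protocol article*

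**What the plan says.** Table 2 gives an item count, response anchors and usually a total-score range for each measure.

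Under Self-regulation, the Emotion Regulation Questionnaire is "a 10-item self-report of emotion regulation strategies, both in how emotions are felt and expressed", with each item answered from 1 to 7. Its scoring entry is "higher total scores (range 10-70) indicate greater tendency to regulate emotions using cognitive reappraisal and expressive suppression strategies". The table mentions no separate score for either strategy.

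Six other rows state these totals:

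- Cognitive control and flexibility (18 items, 1 to 4): "higher total scores (minimum=13, maximum=52) indicate greater daily use of cognitive control and flexibility"
- Memory compensation (12 extracted items, 1 to 5): "higher total scores (minimum=0, maximum=65) indicate greater use of external and internal memory compensation strategies"
- Cognitive activities (10 items, 1 to 5): "higher total scores (minimum=0, maximum=10) indicate greater participation in cognitively stimulating activities"
- Mediterranean diet (16 items, one point each): "range=0-16); higher total scores (minimum=0, maximum=21) indicate greater adherence to the Mediterranean diet"
- Social engagement (10 items, 1 to 6): "higher total scores (minimum=0, maximum=50) indicate greater participation in socially engaging activities"
- Mindfulness (15 items, 1 to 5): "higher total scores (minimum=0, maximum=60) indicate greater use of daily mindfulness activities"

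The Exploratory Analyses section plans paired t tests and Cohen d with 95% CIs for each measure, separately by arm, and associations between mechanisms and outcomes. The Introduction names emotion regulation and cognitive control among the processes through which mindfulness is thought to act. The Objectives put engagement of mechanisms in the secondary aim.

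**The concern.** There are two separate problems.

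The first is a scoring choice. Reappraisal and suppression are different strategies. In a single sum, a gain in one counts the same as an equal gain in the other, and a gain in one is offset by a fall in the other. A null or small effect on the total could therefore mean that neither strategy moved, that one moved and was diluted, or that both moved in opposite directions. These estimates are meant to guide refinement of the program before an efficacy trial that will test mechanisms, so that ambiguity matters.

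The second is that a reader cannot reconstruct several scores from the table. Where the printed range implies a different number of items, or a different item coding, from the rest of the row, it is unclear which score will be analyzed. Change scores, SDs and Cohen d depend on that.

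**Working it through.** **1. Ranges.** Inputs are the item counts, anchors and ranges in Table 2. For k items scored from a to b, a summed score runs from k × a to k × b.

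The rule reproduces three printed ranges, so it suits this table:

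- Emotion Regulation Questionnaire: 10 × 1 to 10 × 7 = 10-70.
- Motivation to change: 27 × 1 to 27 × 5 = 27-135.
- Cognitive Function Index: 14 × 0 to 14 × 1 = 0-14.

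It fails for six:

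| Measure | Items × anchors | Implied | Printed | What would give the printed range |
|---|---|---|---|---|
| Social engagement | 10 × 1-6 | 10-60 | 0-50 | 10 items coded 0-5 |
| Mindfulness | 15 × 1-5 | 15-75 | 0-60 | 15 items coded 0-4 |
| Cognitive activities | 10 × 1-5 | 10-50 | 0-10 | 10 items coded 0/1, or a rescaled sum |
| Cognitive control | 18 × 1-4 | 18-72 | 13-52 | 13 items coded 1-4 |
| Memory compensation | 12 × 1-5 | 12-60 | 0-65 | no item count under 1-5 or 0-4 coding |
| Mediterranean diet | 16 × 0-1 | 0-16 | 0-16 and 0-21 | 0-21 needs 21 one-point items |

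The sleep quality index (9 items, 1 to 4, total 0-21) is not counted, because its row says that it combines scaled and open responses.

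**2. Which conflicts can affect an effect size.** If Y = c + mX with m > 0, the mean change and its SD are both multiplied by m, so their ratio is unchanged. A simulated example (25 people, 15 items) confirms this. The 1-5 sum, the 0-4 sum, the item mean and a linear 0-10 rescale all gave d = 2.759 on the SD of change, d = 0.785 on the average SD, and t = 2.759 × √25 = 13.797 (from the unrounded d).

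The offset for social engagement and mindfulness is therefore harmless to d. Summing 13 rather than 18 items, or reducing a five-point answer to 0/1, is not a linear transformation and can change d.

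**3. The emotion-regulation total.** Let d₁ and d₂ be the effects on reappraisal and suppression in units of their change SDs s₁ and s₂, and r the correlation of the two changes. All five are assumptions, since the article gives no such figures. Then

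d_total = (d₁s₁ + d₂s₂) / √(s₁² + s₂² + 2r·s₁s₂)

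With s₁ = s₂ = 1:

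- d₁ = 0.5, d₂ = 0: 0.5/√1.4 = 0.42 (r = -0.3); 0.5/√2 = 0.35 (r = 0); 0.5/√2.6 = 0.31 (r = 0.3).
- d₁ = 0.5, d₂ = -0.5: numerator 0, so d_total = 0 for every r.
- d₁ = d₂ = 0.5: 0.85, 0.71 and 0.62.

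With s₁ = 1.5 and s₂ = 1, the first case gives 0.49, 0.42 and 0.37, and the second gives 0.16, 0.14 and 0.12. Cancellation is then nearly but not fully complete.

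**The case against.** The strongest reply is that a wrong range in a descriptive table does not alter collected data. The trial is a feasibility study, these analyses are exploratory and within arm, and the Go-No-Go decision uses Table 1, where none of these scores appears. Subscale scoring could also be set out in an analysis plan that is not shown. In the diet row, the one-point-per-food rule agrees with 0-16, and 0-21 may simply have been carried over from the sleep row, although that is a guess.

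Much of this stands. A reader might infer that the mechanism and lifestyle effect sizes are invalid. The article does not support that: two of the six conflicts cannot affect d, and for the other four nothing shows that other items will be summed or responses dichotomized. A reader might also infer that the program should raise reappraisal and lower suppression, so that the total is bound to cancel. The article states no such expectation and gives no split of the 10 items between the strategies. If both strategies rise, the total loses nothing in size.

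What the reply does not remove is that the six rows conflict within themselves, which is a misstatement and not an omission. The emotion-regulation row also defines one total over two named strategies, and that total cannot separate them in any scenario.

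**Conclusion.** The point holds as one of interpretability and of scoring definitions. The emotion-regulation total dilutes a change confined to one strategy (0.5 becomes 0.31 to 0.42) and hides equal and opposite changes entirely, given equal change SDs and a correlation of -0.3 to 0.3. Under a 1.5-to-1 SD ratio the corresponding figures are 0.37 to 0.49 and 0.12 to 0.16.

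Six of the printed ranges do not agree with their own rows. Two are coding offsets without effect on d. Four (cognitive control, memory compensation, cognitive activities, diet) leave the item set or the coding undetermined. The article does not show whether the count, the anchors or the range is the wrong entry, nor that any score will be computed wrongly. The primary benchmarks are untouched, so the importance is moderate at most.

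**What to change.** Analyze cognitive reappraisal and expressive suppression as two scores, state the expected direction of each before the data are examined, and do not rely on the total as the measure of engagement.

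For the six rows, state the items administered, the numerical coding of each response and the matching range. Say explicitly whether cognitive activities are summed as answered, rescaled or dichotomized. Then check the scoring code against the corrected table before the post-intervention analysis.

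This needs no new data or visits, only a table correction and a scoring check. The Results section plans to finish data analysis by December 2025, so the correction belongs before that work. The downside is one additional exploratory mechanism score.

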**Attitudes to change AD/ADRD behaviors**			
	Motivation to Change Lifestyle and Health Behaviours for Dementia Risk Reduction scale [158], a 27-item self-report of attitudes to change behaviors to prevent AD/ADRD	5-point Likert scale ranging from 1=*strongly disagree* to 5=*strongly agree*; higher total scores (minimum=27, maximum=135) indicate greater motivation to alter lifestyle factors and health behaviors to reduce risk of dementia	Moderate to high internal reliability and test-retest reliability in a sample of older adults without dementia [158]
**Exploratory assessments**			
	Multiday Boston Remote Assessment for Neurocognitive Health [159], a 7-day, mobile, self-administered assessment measuring paired associative learning based on everyday objects (signs, groceries, and faces)	Digit-Signs Test (correct number of street sign–number pairings identified), Groceries Prices Test (correct number of grocery-price pairings identified), Face-Name Test (average of correct responses from 2 face-name pairings: first letter name recall and full name recall); higher scores on learning curve (scored over 7 days) indicate better performance (minimum=0, maximum=1)	Good test-retest reliability of the learning curves and excellent reliability between participants’ 2 composite learning curves [160]
	Daily surveys of mindfulness practice (MHB), journaling (HEP^h^), and SCD symptoms (both groups)	Daily mindfulness completed (*yes* or *no*), skills practiced (categorical: all that apply), and time spent practicing these skills (total minutes) in MHB; minutes spent journaling in the HEP [161]; SCD symptoms measured using an 11-point Likert scale ranging from 0=*bad: my thinking is very difficult or slow* to 10=*good: my thinking is sharp and quick* [162,163]	—

^a^Not applicable.

^b^SCD: subjective cognitive decline.

^c^PROMIS: Patient-Reported Outcomes Measurement Information System.

^d^AD/ADRD: Alzheimer disease and Alzheimer disease–related dementias.

^e^MCID: minimal clinically important difference.

^f^CDC: Centers for Disease Control and Prevention.

^g^MHB: My Healthy Brain.

^h^HEP: health enhancement program.

#### Benchmarks

Consistent with NIH stage 1B [62] and pilot study guidelines [76,77], our primary outcomes are a priori markers for feasibility, acceptability, appropriateness, credibility, satisfaction, and fidelity. We set Go–No-Go benchmarks based on similar pilot studies of technology-enabled behavioral interventions for older adult populations [64,70-74].

#### Self-Reported Outcomes

Our selection of self-reported outcomes was guided by our conceptual model (refer to the MHB Intervention subsection), our stage 1 preliminary studies [64-66], and similar lifestyle trials [30,31]. Self-reported outcomes are collected before the intervention, after the intervention, and at the 6-month follow-up during a 60-minute Zoom session. Participants receive a secure link to the self-reported outcomes survey via email from the RA. To aid focus, the RA mutes all participants in the group Zoom session. Participants can use the Zoom hand-raise function or temporarily unmute themselves to seek technical support or ask questions. This system has been used to remotely collect self-reported outcomes for multiple trials of older adults with cognitive impairment [74,83].

#### Repeatable Battery for the Assessment of Neuropsychological Status

The Repeatable Battery for the Assessment of Neuropsychological Status (RBANS) is a comprehensive assessment battery of multidomain cognitive performance [121]. We replaced the Montreal Cognitive Assessment used in our preliminary studies with the RBANS to improve sensitivity to preclinical cognitive changes among older adults with SCD [164-166]. Additional advantages of the RBANS include (1) a total of 4 forms available for repeated assessments to reduce practice effects [167], (2) a comprehensive assessment of 12 subtests in 20 to 30 minutes, (3) strong psychometric properties [168], (4) established telepractice guidelines [169], and (5) administration protocols developed by our team based on similar virtual trials [83].

Trained clinicians administer the RBANS to individual participants via Zoom following a standardized protocol informed by telepractice guidelines [169]. Participants are mailed all testing materials (eg, figure drawing and coding sheets) in advance. Before testing, clinicians ensure that the participants’ environment is optimal (quiet, private, no distractions, writing surface, adequate lighting, etc), internet connection is stable, and audio and video are clear. Participants without access to a large-screen device are provided an iPad to ensure clear visibility of the testing stimuli. Participants mail back their written materials for scoring using a prepaid envelope.

#### Garmin Vivosmart 5 Watch

We selected the Garmin Vivosmart 5 to replace the ActiGraph GT9X. Our preliminary studies revealed that the ActiGraph GT9X is cost prohibitive and frequently had technical support issues that resulted in interrupted data collection and study operations. Additional participant and scientific advantages of the Garmin Vivosmart 5 include (1) its commercial availability and user-friendly design, which promote future scalability; (2) the ability to conduct blinded assessments at study end points by selecting watch faces that do not display step count data; and (3) its reliability and validity for passive monitoring of physical activity and sleep among older adults [170-174]. Our testing showed that step counts measured using the Garmin Vivosmart 5 were internally consistent and produced similar estimates to another widely used device (Fitbit).

The Garmin Vivosmart 5 serves 2 purposes in the RCT. First, in conjunction with the Garmin Connect app, it provides self-monitoring tools (eg, real-time step counting and “move” notifications) to promote engagement in physical activity and sleep [171]. Second, it provides objective, continuous, and passive data to capture within-person changes [175,176] in these lifestyle behaviors during the intervention [177,178]. Wearable devices are both feasible and acceptable for older adults and provide valid measurements of physical activity and sleep [179].

The Garmin Vivosmart 5 is mailed to participants 1 to 2 weeks before the intervention phase, and they set up the watch with the RA during an individual Zoom session. The RA pairs the watch with the participant’s mobile phone and reviews basic instructions (how to wear, charge, and sync). Participants are instructed to wear the Garmin Vivosmart 5 on their nondominant hand for 24 hours per day (except when briefly removing it for charging) to track steps and sleep. The watch is waterproof and can last up to 7 days per charge. Participants sync their data using the Garmin Connect app daily and charge the watch regularly. The RA turns off self-monitoring features (step count and sleep notifications) for blinded before the intervention assessments in both MHB and HEP groups. After the before the intervention assessments are complete, the RA turns on the self-monitoring features in the MHB group only because activity reinforcement is a core component of the technology-enhanced intervention.

Garmin Vivosmart 5 adherence is defined as ≥10 hours of valid wear time based on prior research [180-183]. Wear time is calculated in relation to heart rate by Fitabase [184]. The RA monitors Fitabase and contacts participants after 48 hours of Garmin Vivosmart 5 nonadherence to provide technical support. We estimate a truncated average 7-day step count and sleep data for each participant, measured by the Garmin Vivosmart 5 before the intervention, after the intervention, and at the 6-month follow-up, using an established protocol [71,92,96]. We exclude nonadherent or invalid days of wear as well as the highest and lowest values to reduce the influence of outliers. A minimum of 3 valid days of wear at each time point is required to calculate the averages. Sleep metrics include total hours asleep and sleep efficiency (the ratio of time asleep to time spent in bed) using guidelines for older adults [185]. We visually inspect sleep-wake patterns during the day to exclude naps from the sleep calculations [186].

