**Feasibility**							
	Recruitment and enrollment	Percentage of individuals who participate and enroll from the total contacted		≥70%=good, ≥80%=excellent		Before the intervention	
	Outcome assessments	Percentage of participants with no missing outcome assessment data		≥70%=good, ≥80%=excellent		Before the intervention, after the intervention, and at 6-month follow-up	
	Garmin Vivosmart 5 watch	Percentage of participants who wore the watch at least 5 out of 7 days per week [106,107] for at least 10 hours a day [71]		≥70%=good, ≥80%=excellent		After the intervention	
	Daily surveys	Percentage of participants who completed at least 5 out of 7 daily surveys during the program		≥70%=good, ≥80%=excellent		After the intervention	

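### One 10-hour daily wear rule decides validity for both steps and sleep, so partly worn nights can enter the sleep averages and fully recorded nights can be dropped

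*Protocol article*

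**What the plan says.** The section on the Garmin Vivosmart 5 watch sets out one procedure for both device outcomes:

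- Adherence: "Garmin Vivosmart 5 adherence is defined as ≥10 hours of valid wear time". No time of day is attached. The feasibility benchmark in Table 1 uses the same threshold, "for at least 10 hours a day".
- Detection of wear: "Wear time is calculated in relation to heart rate by Fitabase".
- Averaging: "We estimate a truncated average 7-day step count and sleep data for each participant".
- Exclusion and trimming: "We exclude nonadherent or invalid days of wear as well as the highest and lowest values to reduce the influence of outliers".
- Minimum data: "A minimum of 3 valid days of wear at each time point is required to calculate the averages".

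Two other statements bear on nights. Participants are told to wear the watch "for 24 hours per day (except when briefly removing it for charging) to track steps and sleep". Staff also inspect daytime sleep-wake patterns so that naps do not count as sleep. The sleep metrics are total sleep time and sleep efficiency, scored with reference to cited guidelines. Table 2 gives a benchmark for total sleep time: "MCID=40-minute increase".

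**The concern.** Ten hours of wear at unspecified times is a sensible test of whether a day's steps were captured. It does not test whether a night's sleep was captured, and it can fail in two directions:

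- **Bad nights admitted.** A participant who wears the watch all day and removes it partway through the night passes. The truncated night then enters the average as short sleep.
- **Good nights discarded.** A fully recorded night with little daytime wear totals less than 10 hours and is dropped, although it is the record that the sleep outcome needs.

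The 3-day minimum counts days, so it does not guarantee three usable nights.

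The consequence is error in an outcome that will be read against a 40-minute threshold. Each arm gets its own pre-post comparison, so a change in night wear over time would appear as a change in sleep. Such a change is plausible in MHB: self-monitoring is off in both arms at baseline and then switched on in MHB only, and MHB session 3 teaches participants to track sleep with the watch.

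**Working it through.** The MCID comes from a cited source and is not calculated in the document, so there is no figure of the plan's own to reproduce. The check applies the written rule.

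**Step 1: can the rule misclassify nights?** Assume 8 hours in bed.

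- Waking time is 24 - 8 = 16 hours. Since 16 ≥ 10, a day passes with little or no night wear.
- A night of 7 to 9.5 hours with no daytime wear gives 7 to 9.5 hours in total. This is below 10, so the day is dropped.

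**Step 2: error for one participant.** Let m be the number of valid days and k the number of under-recorded nights (k at least 1 and below m), each short by L minutes and scoring below the good nights. Removing the highest and lowest values leaves m - 2, of which k - 1 are short:

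error = -L × (k - 1) / (m - 2)

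With k = 1 the error is 0, because the bad night is trimmed. With k = 2 (assumption: true sleep 7 h, short nights recorded as 4 h or 3 h, so L = 180 or 240):

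| Valid days m | L = 180 | L = 240 | L needed to exceed 40 min |
|---|---|---|---|
| 7 | -180/5 = -36 | -240/5 = -48 | 40 × 5 = 200 |
| 6 | -180/4 = -45 | -240/4 = -60 | 40 × 4 = 160 |
| 5 | -180/3 = -60 | -240/3 = -80 | 40 × 3 = 120 |
| 4 | -180/2 = -90 | -240/2 = -120 | 40 × 2 = 80 |

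With k = 3 and m = 7, a loss of more than 100 minutes per night suffices (100 × 2/5 = 40). At the 3-day minimum, if it is counted before trimming, one value remains, and two short nights losing more than 40 minutes each are enough.

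**Step 3: group mean.** A simulation of 100,000 participants with 7 valid days assumed true sleep of 420 min, a night-to-night SD of 60 min, and under-recorded nights capturing a uniform 0% to 100% of true sleep. None of these inputs is in the document.

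| Share of valid days with an under-recorded night | Mean bias (min) | Participants with a shortfall above 40 min |
|---|---|---|
| 5% | -5.3 | 2.5% |
| 10% | -11.9 | 8.6% |
| 20% | -28.6 | 26.4% |
| 30% | -48.6 | 46.9% |

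If each such night were instead scored as zero, the mean bias would be -8.4 min at 5% and -22.7 min at 10%. The document does not say how an unworn night is scored.

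**Step 4: effect on a within-arm change.** Equal error at both time points cancels. If under-recording fell from 10% at baseline to 5% at follow-up, the spurious gain would be 11.9 - 5.3 = 6.6 min. From 20% to 5% it would be 28.6 - 5.3 = 23.3 min.

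**The case against.** The strongest reply is that this is a condensed article. It excludes invalid days as well as nonadherent ones without defining the former, and it cites an established averaging protocol and sleep guidelines that may contain a night rule. That possibility stands. However, the article does more than stay silent: it states a rule and applies it to sleep. Neither the nap check nor the 24-hour wear instruction tests whether a given night was worn. Staff contact after 48 hours of nonadherence does not help either, if nonadherence is judged by the same 10-hour definition.

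Other parts of the reply also stand and limit the size. One bad night is trimmed away. Two nights at 4 h among 7 valid days give 36 minutes, which is under the MCID. The wear instruction and a battery life of up to 7 days should make bad nights less common, and the document gives no frequency for them. A wholly unworn night may produce no record, in which case only partly worn nights bias the average.

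A reader might infer that the rule distorts the comparison between arms or the Go–No-Go decision. The documents do not support that. The Exploratory Analyses section analyses the arms separately, no between-arm sleep test is described, and none of the Table 1 benchmarks uses the sleep average.

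**Conclusion.** The point holds as a poorly fitted stated rule for a secondary outcome. As written, one day-level wear criterion governs both steps and sleep; it can admit partly worn nights and discard well-recorded ones.

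For an individual with two or more bad nights, the error can approach or exceed 40 minutes. A reader might go further and conclude that the trial's mean sleep result will be wrong by more than the MCID. The documents do not support that: under the assumed inputs, a mean bias of that size needs somewhere between 20% and 30% of nights under-recorded, and at 5% to 10% it is about 5 to 12 minutes. The practical risk is a shift in night wear between baseline and follow-up within an arm, most plausibly in MHB. All sizes rest on assumed losses and frequencies. The effect on sleep efficiency was not quantified.

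**What to change.** Keep the 10-hour rule for step count and for the wear benchmark. For sleep:

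- Define a valid night as heart-rate-confirmed wear over a night window set independently of the recorded sleep, for example a prespecified clock window or the participant's usual bed-to-wake times, regardless of daytime wear. Requiring wear only across the recorded sleep period would not work: a night cut short by removing the watch can look fully worn over the part that was recorded.
- Treat all other nights as missing.
- Count the minimum in valid nights, say whether it applies before or after trimming, and trim valid nights only.

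If the cited sleep protocol already contains such a night rule, the Garmin section should say that it, and not the 10-hour day rule, governs sleep.

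The cost is a sentence or two and a scoring rule. Wear is already derived from heart rate in Fitabase, so no new data collection should be needed if the timed record is kept. The drawback is that some participants will have too few valid nights and lose a sleep value at a time point.
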